### Statistical methods – analysis population and missing data

Data analysis will be performed based on the original allocation of all patients as defined by randomization, regardless of the degree of adherence to the protocol (intention-to-treat principle). With respect to missing data, the amount thereof, their patterns and the variables associated with omission will define the most appropriate technique to be used in the processing of such data, whether in the primary analysis or the sensitivity analysis. For primary analyses, methods will be used that make use of all available data, such as multiple imputations.

### Monitoring

In addition to the weekly evaluation regarding SSI, all the patients will be instructed to contact the assistant surgeon if they have any issue related to the operation or to the use of the capsules. In case of a diagnoses of SSI or if any problem related to the use of the capsules is recorded, the intake of the capsules will be immediately discontinued and the appropriate conduct will be taken in each case.

### Ethics and dissemination

The study protocol was approved by the institutional ethics committee, and all the subjects signed an informed consent form prior to enrollment.

### Protocol amendments

Any modifications of the protocol that may impact the study, the potential benefit to patients or patient safety, including changes of the study objectives, study design, patient population, sample size, study procedures or other significant aspects will require a formal amendment to the protocol. Such modification shall be agreed upon between the researchers and approval will be obtained from the Research Ethics Committee before implementation.

### Confidentiality

All participant information will be kept in password-protected files with limited access. Data that identify the participants will be replaced by codes.

### Access to data

All researchers involved in the study will have access to all data collected.

### Dissemination policy – authorship

The criteria for authorship of this protocol followed the guidelines established by the International Committee of Medical Journal Editors. A team of professional translators was used to translate the text from Portuguese into English. The final report will follow the main CONSORT 2010 guidelines.

## Discussion

Breast reduction was the eleventh most performed cosmetic procedure in the United States in 2014 (American Society of Plastic Surgeons). It is classified as a “clean operation”, although it has higher rates of infection than other procedures in the same category [18].

Studies comparing factors that affect the occurrence of SSIs in breast surgeries such as smoking, use of a surgical drain, preoperative chemotherapy, breast reconstruction, and associated administration of antibiotic prophylaxis, have presented conflicting conclusions [17, 29, 37, 43–47]. In three SSI cohort studies the recruited patients had differences in risk factors, preventing a quality meta-analysis [17, 43, 48, 49]. Finally, most of the available studies are related to the treatment of breast cancer and not specifically to breast reduction, emphasizing the importance of this study.

We chose to exclude women who have risk factors for SSIs in an attempt to homogenize the sample, allowing us to isolate the postoperative prophylaxis factor. In addition, pre- and intraoperative care related to infection control will be taken, including antiseptic treatment of the operative field, routine antibiotic prophylaxis, hemostasis, care and caution to detachments, handling and preparation of the flaps without tension sutures and sterile dressing will be taken.

Short et al. [18] performed a meta-analysis on SSIs from reduction mammaplasties, and found only three randomized clinical trials. They concluded that preoperative antibiotic prophylaxis is effective in preventing SSIs in reduction mammaplasties; they determined a decrease in the incidence of SSIs of 75%, compared with placebo or no medication, and therefore recommended its use in clinical practice. Their meta-analysis also highlighted the importance of randomized controlled trials to evaluate the postoperative prophylaxis, which has yet to be done [18, 23, 29, 50].

As well as in other studies in which cephalosporins are the main used antibiotics following reduction mammaplasties, we chose to use two different first-generation cephalosporins: cephalothin, for intravenous use in the intraoperative period and the first 24 hours (1 g each 6 hours) and cephalexin for oral use (500 g every 6 hours) in the subsequent postoperative 7 days, compared to placebo [9, 19, 21–23, 27–31].

The objective of the current study is to evaluate the role of antibiotic prophylaxis extended through the postoperative 7 days, in patients who have intraoperative use of cephalothin (every 6 hours, during the first 24 hours), seeking to assess the impact of extended prevention in the SSI rates.

Based on the evidence described and taking into account the study design, the results may justify standard protocols for the use of antimicrobial prophylaxis in breast reduction.

### Trial status

This trial is in the recruiting stage. The first patient was randomized in April 2012; by January 2016, a total of 90 patients had undergone surgery, and none of the patients had any infection during the first 30 days.

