**Methods:**

This is a double-blind randomized clinical trial with 124 breast hypertrophy patients allocated to two treatment groups: antibiotic (*n* = 62) and placebo (*n* = 62). All patients will undergo reduction mammoplasty, performed by the same surgical team. The surgeons will raise the nipple-areola complex by the superomedial pedicle technique. The patients will receive antibiotics intravenously during anesthetic induction and every 6 hours thereafter during their 24-hour hospital stay. During discharge from the hospital, each patient will receive a numbered package containing either cephalexin or placebo capsules and will be directed to take one capsule every 6 hours for 7 days. Neither the surgery team nor the patients will know the contents of the capsules. Patients will be monitored for the occurrence of SSI once weekly during the first 30 days following hospital discharge by a single surgeon who is blinded to their treatment group. SSI will be evaluated based on the definition adopted by the Centers for Disease Control and Prevention.

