The impact of infection on wound healing after breast reduction surgery ranges from minor complications, such as marginal necrosis, which is common at the junction of the inverted “T” incision, to major infections that require surgical intervention [23]. Many surgeons prefer to administer antibiotics, believing that it will reduce the incidence of these problems; however, previous studies suggest that antibiotic prophylaxis fails to reduce the rates of infection in clean surgeries, such as breast reduction [7, 14, 23–26].

Among studies conducted in different countries (United Kingdom, Ireland, Israel, and the United States), there was a tendency to prescribe prophylactic antibiotics beyond the intra- and postoperative periods (24 hours) of breast reduction, ranging up to 14 days. Cephalosporins were the most frequently prescribed, with the exception of the UK, which mentioned the use of amoxicillin/clavulanic acid in 70% of cases [9, 19, 21–23, 27–31].

Veiga-Filho et al. [32] compared SSI rates in patients receiving cephalexin for 7 days after hospital discharge (24 hours after breast reduction surgery) to patients who did not receive antibiotics. They observed significantly higher SSI incidence rates in the control group compared with the experimental group receiving antibiotics (14% vs. 2%, respectively; *p* = 0.03). They also observed that the incidence of SSIs was greater in older patients and in patients with a greater resected breast tissue mass (*p* = 0.02; *p* = 0.04, respectively) [32].

Reduction mammaplasty is an effective procedure that improves the quality of life for women with breast hypertrophy and is one of the most common plastic surgery procedures [33–36]. Prevention of SSIs is extremely important, because infection may compromise the outcome of the procedure, and increase the length of stay and costs of hospitalization [37].

This study was designed to address the lack of consensus on the role of antibiotics in breast reduction surgery. Despite the absence of solid evidence, the use of antibiotics following reduction mammaplasty is widespread, and a previous nonrandomized trial demonstrated higher SSI rates when no antibiotics were used. Thus, this trial was designed to compare the effectiveness of antibiotics prophylaxis for 24 hours with the extended use of antibiotics for 7 additional days.

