### Sample size

The experimental and control groups were designed for 62 patients each to ensure a significance level of 5% and power of 80%. This was calculated based on the proportions observed in a previous study with and without the use of antibiotics after breast reduction [32].

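### With no infections in the first 90 of 124 patients, the 14% vs 2% planning rates and the stated 80% power no longer hold, and the tests named for the SSI comparison are uninformative at zero events

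*Protocol article*

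**What the plan says.** Sample size (Protocol article) gives 62 patients per arm, 5% significance and 80% power, and says of the basis: "This was calculated based on the proportions observed in a previous study with and without the use of antibiotics after breast reduction". The Background reports that study's infection rates, control against antibiotic, as "14% vs. 2%, respectively".

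Trial status, written while recruitment was still open, reports that "by January 2016, a total of 90 patients had undergone surgery, and none of the patients had any infection during the first 30 days".

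Statistical methods – outcomes names the chi-square test or Fisher's exact test for comparing SSI between the arms. It names no effect estimate or interval for that comparison.

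The Discussion closes by saying that "the results may justify standard protocols for the use of antimicrobial prophylaxis in breast reduction". Protocol amendments provides a formal route for changing the sample size or design. No section returns to the planning rates after the zero count.

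**The concern.** The power statement and the data that undermine it stand in the same article. Power of 80% is a property of the design only if roughly 14% of placebo patients become infected, and almost three quarters of the sample (90/124 = 73%) has been operated on without one infection.

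Two things are at stake. First, the trial will very probably end with zero or a handful of events, so the planned test has almost no chance of detecting anything. Second, a p-value near 1 from such a table does not say how large a benefit of the antibiotic has been excluded. Without a stated bound, a null result from a trial described as having 80% power could be taken as firmer evidence against extended prophylaxis than it is.

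**Working it through.** **Inputs.** Rates of 14% (control) and 2% (antibiotic), from the Background. 62 per arm, 5% significance and 80% power, from Sample size. 0 SSI in 90 patients, from Trial status, so 124 − 90 = 34 remain. The split of the 90 by arm is not disclosed. I assume 45/45, hence 17/17 remaining. With 62 per arm, the number of placebo patients among the 90 can lie only between 28 and 62.

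**1. The plan's own figure.** Pooled two-proportion formula, mean rate 0.08:

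n = [z_α·√(2·0.08·0.92) + 0.842·√(0.14·0.86 + 0.02·0.98)]² / 0.12²

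- One-sided 5% (z = 1.645): 62.1, that is 63 (61 with unpooled variance), so the stated 62 is matched.
- Two-sided 5% (z = 1.960): 79.0, that is 80. Two-sided power at 62 per arm is about 70%.

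The 62 therefore follows from 14% vs 2% on a one-sided reading. Sidedness is not stated, and nothing below depends on resolving it.

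**2. Are 14% and 2% compatible with 0/90?** P(0 events) = 0.86^k × 0.98^(90−k), with k placebo patients among the 90.

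| k | P(0/90) |
|---|---|
| 28 (most favourable to the plan) | 0.0042 |
| 45 (assumed) | 0.00045 |
| 62 | 0.00005 |

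If some late patients had not completed 30 days, little changes: with 80 complete and evenly split, 0.86^40 × 0.98^40 = 0.0011.

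**3. What rate is compatible?** The exact two-sided 95% upper limit is 1 − 0.025^(1/90) = 4.0%. The planned average was (14 + 2)/2 = 8%.

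**4. What would be significant at 62 vs 62?** Two-sided p-values with no antibiotic-arm infection:

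| Placebo vs antibiotic SSIs | Fisher | Uncorrected chi-square |
|---|---|---|
| 3 vs 0 | 0.244 | 0.080 |
| 4 vs 0 | 0.119 | 0.042 |
| 5 vs 0 | 0.057 | 0.022 |
| 6 vs 0 | 0.028 | 0.012 |

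Fisher needs 6 vs 0 and chi-square 4 vs 0, all among the last 34 patients.

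**5. Chance of getting there.** Sum Bin(a; m, p_C) × Bin(b; 34 − m, p_A) over all a, b whose final table a/62 vs b/62 has p < 0.05, where m is the number of placebo patients left.

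| Rates | m | Fisher | Chi-square |
|---|---|---|---|
| 14% vs 2% | 12 | 0.2% | 4.8% |
| 14% vs 2% | 17 | 1.7% | 14.8% |
| 14% vs 2% | 22 | 6.2% | 29.7% |
| 5% vs 1% | 17 | 0.01% | 0.7% |

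The 5% vs 1% pair is illustrative; its average of 3% lies below the 4.0% limit.

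**6. What a final 0/62 vs 0/62 would show.** Fisher gives p = 1, and chi-square is undefined because an expected count is zero. The Wilson upper limit per arm is z²/(n + z²) = 3.84/65.84 = 5.8%, so the Newcombe 95% interval for the difference is 0 ± 5.8 points. The exact upper limit per arm is 1 − 0.025^(1/62) = 5.8%.

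**The case against.** **The zero count is openly reported, and a null result would still be informative.** Both are true. At 0 vs 0 the interval of ±5.8 points excludes the 12-point difference on which the trial was sized. It does not exclude smaller benefits, and the power statement remains uncorrected.

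**An article may leave estimates and intervals to a fuller plan, and the final report is to follow CONSORT 2010.** This stands in part. A reader might infer that the trial will report p-values and nothing else; the document does not say so. It shows only that the article names tests alone for this comparison. Those tests cannot inform at zero events, so naming the interval as the primary result is still an improvement on what is written.

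**Significance is not equally remote under both tests.** Correct. Quoting Fisher alone would overstate the case, because uncorrected chi-square needs only 4 vs 0. Fisher is the natural choice with so few events, and at rates compatible with 0/90 both chances are negligible for near-even splits.

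**Selection of patients.** The Discussion says "We chose to exclude women who have risk factors for SSIs in an attempt to homogenize the sample", and a reader might conclude that this pushed the infection rate below that of the sizing study. The earlier study's eligibility criteria are not in the documents, and it may have had similar exclusions. The cause of the low rate is left open here.

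**The closing claim.** A reader might take it as a promise to settle practice, or as a claim that a null result proves antibiotics unnecessary. The wording is conditional, and the article nowhere claims equivalence or non-inferiority.

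**Conclusion.** The point holds. The 80% power rests on rates that the trial's own data contradict under every possible split of the 90 patients (probability 0.00005 to 0.0042), so the design no longer has that property. At an assumed 17/17 split of the remaining patients, the chance of significance at the planning rates is 1.7% (Fisher) or 14.8% (chi-square), and it is below 1% under either test at 5% vs 1%. These conditional figures depend on the assumed split; the rejection of the planning rates does not. What the trial can still deliver is a bound on the difference of roughly 6 percentage points if no infections occur. It would be wrong to say that significance is impossible, or that the low rate has been traced to the eligibility criteria.

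**What to change.** Use the route in Protocol amendments. The pooled zero count is already published, so no unblinding is involved.

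1. **Sample size:** keep the existing justification and add a dated note that the 14% vs 2% assumption and the 80% power no longer hold after 0/90. Give the attainable precision: about ±5.8 points at 0/62 vs 0/62, which excludes the planned 12-point difference but not smaller benefits.
2. **Statistical methods – outcomes:** make the primary result the SSI risk difference with a 95% confidence interval (Newcombe or Miettinen-Nurminen) and an exact upper limit per arm, with Fisher's p-value alongside.
3. **Discussion:** qualify the closing sentence so that a null result is interpreted only up to the upper confidence limit, and not as proof of no benefit.

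The cost is amendment wording and one interval calculation, with no added patients. The downside is a more modest claim.

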## Abbreviations

BMI: body mass index
CDC: Centers for Disease Control and Prevention
SSI: surgical site infection
